## Results

### Statistical analysis

We will conduct two sets of statistical analyses. The primary analysis will be an intention-to-treat analysis, whereby participants are analysed in the arm of the trial they were randomised to, regardless of how many sessions of the programme they attend. In order for an intention-to-treat analysis to be conducted, we will endeavour to collect outcome measures for everyone (while recognising the right of participants to withdraw from the trial at any stage). The secondary analysis will be conducted on a "per protocol" basis. This analysis will exclude participants who attend fewer than four sessions of the fatigue management programme.

Data will be analysed primarily using SPSS for Windows. A 5% significance level will be used. Outcome measures will be assumed to be interval scaled, and the analysis will initially be focused on absolute change in outcome post-intervention relative to baseline, and absolute change in outcome at 4- and 12-month follow-up, relative to baseline. These change scores, presented separately for the three follow-up periods, are being used because we think they are the most clinically useful. They are likely to be normally distributed (this assumption will be checked). Change scores will be compared between the two groups using the independent samples *t*-test.

Additional analyses will be conducted to address the following issues:

1. We will adjust for baseline variability/baseline differences between treatment arms. For each outcome variable analysed, these would include the baseline measurement for that outcome, baseline primary outcome measures, gender, age, marital status, education level, type of MS, time since diagnosis, and level of disability.

2. Although participants in the trial have been randomised individually, for those randomised to the fatigue management intervention, it is possible that the group-based nature of the intervention will result in observations that are clustered. This could result in misleading statistical tests [74]. We will assess the extent to which this occurs by incorporating clustering into the analysis.

3. It is likely that outcome data will be missing for some participants. In the main analysis such individuals will be excluded. However, the implied assumption that the data are "Missing Completely At Random" might not be correct, potentially leading to biased estimates of the effect of the intervention [75]. Two methods will be used to assess the extent to which this occurs: Firstly, we will use the "Last Observation Carried Forward" imputation method (which assumes no change in outcome when a data point is missing). Secondly, we will use a mixed model for repeated measurements.

4. Analysing the change in outcome from baseline to each time point will, we believe, result in the most clinically useful presentation of results. However, to gain a deeper understanding of how outcome measures change over the course of follow-up, we will also model all measurement occasions together for each outcome.

5. It is possible that the fatigue management programme might be more effective in certain sub-groups of individuals. We will examine these potential effect modifiers by testing the relevant "treatment x effect modifier" interaction terms. However, we acknowledge that these statistical tests are likely to be underpowered, since this was not a specific aim of the study. In these analyses, we will consider study centre, baseline fatigue, gender, age, marital status, type of MS, time since diagnosis, and level of disability.

These additional analyses will involve the use of a variety of techniques including multi-level/mixed models. In addition to these pre-specified analyses, we will also conduct further exploratory analyses as suggested by the data.

Presentation of the results will follow the Consolidated Standards of Reporting Trials (CONSORT) [76,77] guidelines, in such a way that they can be meaningfully incorporated into systematic reviews. The design of the trial will help ensure that it is graded as high quality in systematic reviews.

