### Intervention

The group-based fatigue management intervention [45] is based upon a conceptual framework that integrates elements from cognitive behavioural [70], social-cognitive [71], energy effectiveness, self-management [72] and self-efficacy [73] theories.

The intervention focuses on the management of fatigue, the most common symptom of MS, and is likely to be relevant to many people. However, it is expected that it will also provide a framework to help people manage their MS more generally. A cognitive behavioural approach that focuses on one symptom is likely to be clearer and less overwhelming than one encompassing many aspects, can be achieved in a smaller number of sessions, and will be easier to integrate within existing services.

The intervention consists of six sessions held on a weekly basis; the first, 2 hours' duration, and subsequent sessions, 1.75 hours' duration (each with a 15 minute refreshment break halfway through). It is designed to be run by two health professionals with experience of working with people with MS and of group-work (such as occupational therapists, nurses, or physiotherapists). This latter feature enables the intervention to be incorporated into existing health service structures. The intervention will be delivered to groups of 6-12 people.

Participants are encouraged to bring along a "supportive other" to the first session. Since the intervention entails participants making lifestyle changes, the involvement of a "supportive other" could help to encourage and support them in making such changes. Contact between members of the group outside the formal group setting will be encouraged, as an additional source of support.

The intervention is manualised and sessions are delivered via PowerPoint. A summary of programme content is presented in Table 1. The facilitator manual (~100 pages) provides detailed session information, guidance on preparation and delivery, a checklist of facilitator objectives and signposts to additional resources. There is also a companion participant workbook to reinforce material from the programme. Facilitators will be trained at one day orientation workshops and psychological advice and debriefing will be available for facilitators throughout the trial.

**Table 1 T1:** Summary of content of the Fatigue Management Programme

Session	Title	Content	Homework

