#### Missed sessions

If participants do not attend a session they will be sent the materials they missed and, where possible, the session will be held over the telephone. Participants receiving the intervention will continue to have access to services available as part of their usual local care.

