### Control group

Participants randomised to this arm of the trial will receive current local practice. Inevitably, there will be minor variations in the exact composition of what is usually provided, both within and between centres; depending on local resources and patient need. We consider this minor variation in current local practice to be a strength of the trial as it will increase the applicability of the findings to a wider range of centres. Individuals who have recently received substantive fatigue management are not eligible for the trial (see exclusion criteria).

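### The secondary per-protocol analysis removes low attenders from the programme arm only, so it sets selected attenders against unselected controls and may be biased in either direction

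*Protocol article*

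**What the plan says.** The Statistical analysis section of the protocol article plans two sets of analyses. For the first: "The primary analysis will be an intention-to-treat analysis, whereby participants are analysed in the arm of the trial they were randomised to", whatever their attendance. The second, called secondary and per-protocol, carries one rule: "This analysis will exclude participants who attend fewer than four sessions of the fatigue management programme". The main test is also fixed there: "Change scores will be compared between the two groups using the independent samples" t-test, unadjusted. Adjustment for baseline variables is listed as an additional analysis, and the article does not say whether it extends to the per-protocol set.

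Three other sections bear on the rule:

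- Intervention: "The intervention consists of six sessions held on a weekly basis", so the threshold is four of six.
- Control group: "Participants randomised to this arm of the trial will receive current local practice". No criterion for this arm corresponds to the attendance rule.
- Missed sessions: for those who miss one, "they will be sent the materials they missed and, where possible, the session will be held over the telephone". The article does not say whether a telephone session counts as attended.

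**The concern.** Attendance is observed after randomisation and in one arm only. Applied to controls, the rule would remove all of them, which cannot be meant. What remains is FMP attenders against the whole control arm. The people in the control arm who would have attended poorly, had they been offered the programme, stay in the comparison while their FMP counterparts leave it. The two groups are then no longer those that randomisation made comparable.

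The article itself gives reason to think that attendance and outcome are linked. Under the ethical and management considerations, venue and session length are planned around participants' fatigue. The exclusion criteria remove people with a recent relapse because it could change fatigue in its own right. A relapse during the six programme weeks could both reduce attendance and move the change score.

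What is at stake is the pre-specified secondary estimate. It could show a difference when the programme has no effect, or hide part of a real one.

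**Working it through.** **The plan's own figure.** Sample size section: medium standardised effect (0.5), two-sided 5%, 85% power, 73 per arm. The normal approximation gives n = 2 × (1.960 + 1.036)² / 0.5² ≈ 72 per arm. The t-test version gives 72.8, so 73, with power 85.1%. The figure reproduces. With 180 enrolled and 20% missing, 180 × 0.8 = 144, or 72 per arm, are analysable. These 72 are used below.

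**Inputs not in the article (assumed).**
- q: share of FMP participants with outcome data who fall below four sessions; range 10% to 30%.
- D: mean change attenders would show minus that of low attenders, with no programme effect, in SD of the change score; range −0.5 to +0.8. Positive means attenders do better.

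**Bias formula.** With no programme effect, the expected control mean equals the full FMP-arm mean, (1 − q) × m_att + q × m_low. The per-protocol contrast uses m_att instead. The difference is q × (m_att − m_low) = q × D.

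**Rejection rate with no true effect.** SE = √(1/(72(1 − q)) + 1/72). For q = 20% and D = 0.5: bias = 0.10; SE = √(1/57.6 + 1/72) = 0.177; bias/SE = 0.566; P(Z > 1.96 − 0.566) + P(Z < −1.96 − 0.566) = 0.0816 + 0.0058 = 8.7%.

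Bias in SD, with the two-sided rejection rate of the nominal 5% test for positive D:

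| q | D = −0.5 | D = −0.25 | D = 0 | D = 0.25 | D = 0.5 | D = 0.8 |
|---|---|---|---|---|---|---|
| 10% | −0.05 | −0.025 | 0 | 0.025 (5.2%) | 0.05 (6.0%) | 0.08 (7.5%) |
| 20% | −0.10 | −0.05 | 0 | 0.05 (5.9%) | 0.10 (8.7%) | 0.16 (14.8%) |
| 30% | −0.15 | −0.075 | 0 | 0.075 (6.9%) | 0.15 (12.9%) | 0.24 (25.7%) |

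A bias of 0.10 SD is one fifth of the 0.5 SD target.

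**Why a negative D is possible.** The outcome is change from baseline. Suppose low attenders start 0.5 SD worse and the baseline-to-follow-up correlation r is 0.5 to 0.7 (assumed). Regression to the mean then gives them an extra untreated improvement of 0.5 × (1 − r) = 0.25 to 0.15 baseline SD. Removing them would bias the contrast against the programme.

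**The case against.** The strongest defence is that little rests on this analysis. It is declared secondary, the primary analysis keeps everyone as randomised, and the sample size does not depend on it. That stands, and it limits the weight of the point. It does not repair the contrast.

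Four stronger readings may tempt a reader, and the article does not support them.

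- *The analysis favours the programme.* Neither q nor D is given. Poorer prognosis in low attenders is plausible, but because change scores are analysed, a worse starting level does not by itself imply worse change. People might also stop because they feel better.
- *The share removed equals the share of low attenders.* Low attenders may also fail to return questionnaires, and the main analysis already leaves out people without outcomes. The extra share removed could be smaller, which is why q is defined among those analysed.
- *People who took sessions by telephone are discarded as untreated.* The rule is silent on telephone sessions; it does not exclude them. Taken alone, that is a detail a condensed article may leave to the full plan.
- *A complier-average analysis is simply right and should displace the per-protocol one.* It assumes that allocation does nothing for people below the threshold. Here they may attend up to three sessions and receive posted materials. If they benefit as much as attenders, dividing a 0.5 SD intention-to-treat effect by 0.9 to 0.7 gives 0.56 to 0.71 SD, which is 0.06 to 0.21 SD too large. This limits how the estimate may be read, although the method stays valid when there is no effect.

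Baseline adjustment could reduce the selection if applied to this set. It cannot reach motivation or events after baseline.

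**Conclusion.** The point holds for the secondary analysis. The stated rule selects on a post-randomisation variable in one arm, no matching criterion or correction is given, and the resulting contrast is not a randomised one. It may be biased in either direction, plausibly towards the programme if low attenders would have done worse anyway.

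The size is conditional. For q of 10% to 30% it is zero at D = 0, +0.05 to +0.15 SD at D = 0.5 SD, and −0.05 to −0.15 SD at D = −0.5 SD. Both q and D are assumptions, so no single figure can be called the bias of this trial. The loss of comparability is certain; its sign and size are not. The primary intention-to-treat conclusion is untouched. The change is worth making because it is cheap, but the trial does not depend on it.

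**What to change.** Estimate the effect of attendance with a complier-average causal effect analysis: randomised arm as the instrument for receiving at least four sessions, baseline-adjusted (for example by two-stage least squares), with everyone kept in the arm to which they were randomised. If the four-session per-protocol comparison is kept, report it only as a supportive, non-randomised analysis.

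Add two sensitivity analyses: a lower threshold (any session received), and telephone sessions counted as received. State before outcome data are seen which definition is the main one.

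The cost is modest: the attendance data that the per-protocol rule already needs, and a little more analysis. Intervals are wider. At q = 20%, treating q as known and ignoring covariates, the SE is about √(2/72) / 0.8 = 0.167 / 0.8 = 0.208 SD, against 0.177 for the per-protocol contrast. The exclusion restriction is strained by partial attendance and by posted or telephone material, so the estimate may be too large if low attenders also benefit. The lower threshold shows how far that matters, and the report should say so.

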### Participants

#### Sample size

Sample size consideration is mostly based upon fatigue as the primary outcome measure; this is the outcome measure used most frequently in other trials that include people with fatigue. As a variety of fatigue measures have been used in other trials, we have used standardised effect sizes to enable comparisons between them. Standardised effect sizes of 0.2 are commonly considered small, 0.5 considered medium, and 0.8 considered large [47]. In this trial, we will aim to detect a medium effect size. The Cochrane systematic review of cognitive behavioural therapy in people with CFS [38] identified two good quality studies, and in these the standardised effect sizes for fatigue were 0.7 and 1.0. The Cochrane Systematic Review of Amantadine for fatigue in MS found effect sizes of between 0.3 and 1.4 for the three studies that measured fatigue on a continuous scale [21]. Thus, our choice of an effect size seems reasonable in the context of (a) how well cognitive behavioural approaches work in another chronic disease where fatigue is a major symptom, and (b) how well another treatment for fatigue works in MS. For 85% power, the sample size requirement (using a two-tailed 5% significance level) is 73 people per arm of the trial; 146 in total. Inevitably, there will be some participants who withdraw from the trial during its course, or more generally, do not complete outcome measures. To allow for this, we will aim to enrol 180 participants; 90 in each arm of the trial. Thus, if 20% of participants do not provide data on the primary outcome measures, the study would maintain statistical power. This figure of 20% will be reviewed during the study and sample size adjusted up or down accordingly.

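### The main analysis is an unadjusted t-test of change from baseline; making the baseline-adjusted difference (ANCOVA) primary would be a free improvement in precision, of uncertain size

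*Protocol article*

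**What the plan says.** The Statistical analysis section of the protocol article states that "the analysis will initially be focused on absolute change in outcome post-intervention relative to baseline", with the same approach at 4 and 12 months. The three follow-ups are presented separately, and arms are compared by an independent-samples t-test on the change scores. The reason given is clinical usefulness; precision is not mentioned.

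The first item under the additional analyses reads "We will adjust for baseline variability/baseline differences between treatment arms". The covariates for each outcome are its own baseline value, the primary outcomes at baseline, and a list of demographic and disease variables.

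Under Outcome Measures, outcomes are measured one week before the programme starts, so the covariate is already collected.

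Under Sample size, the authors explain that "we have used standardised effect sizes to enable comparisons between them" and state "In this trial, we will aim to detect a medium effect size", having defined medium as 0.5. They do not say whether the SD behind that 0.5 is that of the follow-up score or of the change score, and they give no baseline/follow-up correlation.

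**The concern.** A change score subtracts the whole baseline value, which fixes the baseline slope at 1. When the true slope is below 1, as regression to the mean usually makes it, this subtracts too much. An arm that starts higher by chance then appears to improve more than it should. ANCOVA estimates the slope from the data, removes that shift and leaves a smaller residual variance. What is at stake is the precision of the main result, and its sensitivity to chance imbalance between arms of about 73. Validity is not at stake.

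**Working it through.** **Inputs from the document (Sample size).** Two-sided 5% level, 85% power, standardised effect 0.5, 1:1 allocation, 73 per arm. **Assumed, because not given:** the baseline/follow-up correlation r, taken over 0.3 to 0.9, and the ratio of follow-up to baseline SD.

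**Step 1: the plan's own figure.** An exact two-sample t calculation for effect 0.5 needs 72.80, so 73 per arm, with power 85.1%. The normal approximation gives 72 per arm, and 85.6% power at 73. The stated 73 per arm reproduces.

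**Step 2: variance with equal SDs (σ).**
- Change score: 2(1−r)σ²
- ANCOVA on own baseline: (1−r²)σ²
- Ratio: (1−r²)/[2(1−r)] = (1+r)/2

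| r | ratio | fall in standard error |
|---|---|---|
| 0.3 | 0.65 | 19.4% |
| 0.5 | 0.75 | 13.4% |
| 0.7 | 0.85 | 7.8% |
| 0.9 | 0.95 | 2.5% |

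**Step 3: power at 73 per arm, equal SDs, no clustering (normal approximation).** The two readings of 0.5 differ:
- In change-score SD units, the planned t-test has 85.6% at every r. ANCOVA has 96.3% (r = 0.3), 93.7% (0.5) and 90.6% (0.7).
- In follow-up SD units, change score against ANCOVA is 72.3% against 88.6% (r = 0.3), 78.7% against 90.9% (0.4), 85.6% against 93.7% (0.5) and 92.2% against 96.5% (0.6).

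ANCOVA is ahead under both readings. The t-test falls below its stated power only under the second reading, and only when r is below 0.5.

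**Step 4: unequal SDs.** Let k be follow-up SD over baseline SD, with baseline SD 1. The change-score variance is k² + 1 − 2rk, and the ANCOVA variance is k²(1−r²). They differ by (1−rk)², which is never negative but is zero when rk = 1. For example, k = 1.25 and r = 0.8 gives a ratio of 1.00, so no gain. With k = 0.8 and r = 0.5 the ratio is 0.571, a larger gain than the equal-SD formula gives.

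**Step 5: why k may exceed 1 here.** Eligibility requires a Fatigue Severity Scale score above 4, and the primary fatigue subscale shares eight of that scale's nine items. Selection on nearly the same scale tends to narrow the baseline spread. As an illustration, assume SDs of 1 and r = 0.6 before selection, with a linear relation (slope 0.6, residual variance 1 − 0.36 = 0.64).
- Baseline variance halved: follow-up variance 0.36×0.5 + 0.64 = 0.82; change variance 0.82 + 0.5 − 2×0.3 = 0.72; ratio 0.64/0.72 = 0.89. The within-trial r is 0.47, for which the equal-SD formula would give 0.73.
- Baseline variance cut by 30%: follow-up variance 0.892; change variance 0.892 + 0.7 − 2×0.42 = 0.752; ratio 0.64/0.752 = 0.85, where the formula would give 0.77.

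In this illustration the saving is about 11-15% of variance.

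**Step 6: chance imbalance.** At 73 per arm the baseline difference between arms has standard error √(2/73) = 0.17 SD. With equal SDs and r = 0.5, an imbalance of 0.2 SD moves the change-score estimate by (1−0.5)×0.2 = 0.1 SD, one fifth of the target effect. ANCOVA removes that shift.

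**The case against.** The strongest reply is that nothing here is an error. The t-test is valid and unbiased under randomisation, its rationale is stated, and adjustment for the outcome's own baseline is pre-specified, as are models of all measurement occasions together. Only the ranking of two planned analyses is at issue, and the gain depends on quantities that the document does not give. All of this stands, and it limits the point to an improvement. It gives no reason to keep the unadjusted test first. Regressing change on arm and baseline gives the same treatment effect as regressing the follow-up score, in the same units, so the clinical reason for change scores is preserved.

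Three stronger readings are tempting, and the document does not support them:
- A reader might infer that the trial is already short of its stated power. Apart from clustering, 180 × 0.8 = 144, or 72 per arm, gives 84.6% by exact t against 85.1% at 73, and the text says the 20% loss figure will be reviewed and the sample size adjusted. The larger losses in Step 3 need both follow-up SD units and r below 0.5, neither of which is stated. Above r = 0.5 on that reading, the t-test exceeds 85%.
- A reader might infer that two rival headline results will exist. The text separates a main analysis from additional ones, so the order is clear.
- A reader might count possible clustering within programme groups here. It is a separate matter, which the plan lists as its own item and ANCOVA does not solve.

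**Conclusion.** The point holds as a free improvement to the choice of main analysis. In large samples ANCOVA on the outcome's own baseline is never less precise than the planned change-score test, and it avoids over-correcting chance imbalance. With equal SDs the variance falls by 35%, 25% and 15% at assumed r of 0.3, 0.5 and 0.7. If selection at entry narrows the baseline SD, 10-15% is more realistic for fatigue, and the gain can be close to nil. The direction is firm. The size is not, because it rests on a correlation and an SD ratio that are absent from the document. No bias, invalidity or demonstrated power shortfall follows.

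**What to change.** State that the primary estimate at each follow-up is the baseline-adjusted mean difference: change (or follow-up score) regressed on arm, with that outcome's own baseline and centre as covariates. Centre belongs in the model because allocation is stratified by it. Keep the long covariate list of the first additional item out of the primary model and leave it as an additional analysis. Tabulate raw mean changes by arm for clinical readers, and keep the unadjusted t-test as supportive. The cost is wording and a few degrees of freedom: the baselines are already collected, and adjusted models are already planned, though with a longer covariate list.

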### Outcome Measures

The following demographic information will be collected before the start of the trial: age, sex, educational attainment, marital status, number of children, length of time since diagnosis, disease course, relapse history, employment status, prescribed drugs currently taken, co-morbid medical conditions, disability level.

For those randomised to the FMP, outcomes will be measured 1 week prior to the start of the programme and 1 month, 4 months and 12 months after the end of the programme. For those randomised to current local practice, outcomes will be sent on the same dates as those randomised to the FMP.

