### Primary Outcome Measures

These are all self-reported questionnaire measures and specified *a priori*.

There are three primary outcomes:

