#### Data Collection

Trial data will be used to consider the relative effectiveness of the intervention versus comparator, and primary and secondary outcome measures have been described above. Patient level data will be collected within the trial both pre- and post-intervention, and at 4- and 12-month follow-up for those in the fatigue management arm of the trial and equivalent time points post-randomisation for those receiving current local practice. The primary economic analysis of outcomes will be between baseline and 4-month follow-up, although analysis using the shorter time horizon, and other longer term modelled outcomes will also be presented.

Resource use data will be collected over the 4-month follow-up period and will primarily comprise the direct delivery of the group-based cognitive behavioural approach (e.g. staff time, related consumables, and any travel costs for the health professional). Record forms will be used by staff delivering the intervention to identify staff time used, and the main categories of staff time (e.g. delivery of sessions, preparation, setting-up) and semi-structured interviews will be held with each of the Service Providers (centres) to estimate the broader resource use associated with delivery of the intervention.

Further data on NHS and personal social services resource use (e.g. related hospitalisation, Accident and Emergency Department visits, and General Practitioner visits) and information on carer time will be gathered using a simple patient self-completion questionnaire (completed at 4- and 12- month follow-up), and differences between groups will be investigated and reported as part of the economic analysis.

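### Three co-equal primary outcomes are each tested at three follow-ups at 5%, with no primary visit and no decision rule, while the sample size covers a single test based mostly on fatigue

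*Protocol article*

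**What the plan says.** All references are to the protocol article.

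- **Primary Outcome Measures:** "There are three primary outcomes". They are the FAI fatigue severity subscale, the MSIS-29 total and the MS-FSE, with no ranking among them. The Primary aim puts all three into one sentence.
- **Outcome Measures:** follow-up is at "1 month, 4 months and 12 months after the end of the programme".
- **Statistical analysis:** "A 5% significance level will be used", and "Change scores will be compared between the two groups using the independent samples" *t*-test. On the visits it says "These change scores, presented separately for the three follow-up periods, are being used because we think they are the most clinically useful".
- **Sample size:** "Sample size consideration is mostly based upon fatigue as the primary outcome measure", and "In this trial, we will aim to detect a medium effect size", which that section equates with 0.5. The only calculation gives 73 per arm (146 in total) for 85% power with a two-tailed 5% test. No visit is mentioned.
- **Economics evaluation, Data Collection:** "The primary economic analysis of outcomes will be between baseline and 4-month follow-up". This is the only place where a follow-up is called primary.

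**The concern.** Three outcomes at three visits give nine tests, and each carries the primary label and the full 5%. The article does not say whether one significant result is enough, whether all three outcomes must be positive, or at which visit. The stated 5% therefore describes each test and not the conclusion on the primary aim.

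The sample size has the same gap. It speaks of fatigue as the primary measure, in the singular, and powers one test of it. The stated 85% does not describe a conclusion that depends on three outcomes.

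The Discussion frames the trial as answering whether the intervention has a significant impact on fatigue, self-efficacy and quality of life. A reader of the results would need to know beforehand what counts as a yes.

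**Working it through.** **1. Reproduce the sample size.** Inputs from Sample size: d = 0.5, two-sided alpha 0.05, power 0.85, equal arms.

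Normal approximation: n per arm = 2(1.960 + 1.036)² / 0.5² = 71.8, so 72. The exact two-sample t calculation gives 72.8, so 73. Power at 73 per arm is 85.1%. The stated figure is right, and it is the figure for one outcome tested once.

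**2. Count the primary tests.** 3 outcomes × 3 follow-ups = 9, each at 0.05.

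**3. Family-wise error if any one of the nine counted as success, with no true effect anywhere.**

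Independent tests: 1 − 0.95⁹ = 37.0%. This is a ceiling, because the tests share participants and each outcome's change scores share a baseline. If variances are equal and every pair of occasions has the same correlation ρ, two change scores from one baseline have covariance 1 − ρ and variance 2(1 − ρ), so they correlate 0.5 whatever ρ is.

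The article gives no correlations, so the values below are assumptions. The results come from simulated multivariate normal test statistics (400,000 draws), with the correlation between two tests taken as the product of the outcome and visit correlations.

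| Correlation between outcomes / between visits | At least one false positive in nine |
|---|---|
| 0 / 0 | 37% |
| 0 / 0.5 | 33% |
| 0.5 / 0.5 | 29% |
| 0.7 / 0.7 | 23% |
| 0.9 / 0.9 | 14% |

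**4. Three outcomes at a single visit.** Independent: 1 − 0.95³ = 14.3%. At correlation 0.5 it is about 12.5%, and at 0.7 about 11%.

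**5. The opposite rule, that all three outcomes must be significant at one visit.** The false-positive rate is then no higher than 5%, but power falls. With d = 0.5 on every outcome and independent tests it is 0.851³ = 62%. Positive correlation raises this towards 85%, which is reached only if the three tests always agree.

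**6. Power if alpha is split over three outcomes.** Alpha = 0.05 / 3 = 0.0167, d = 0.5, 73 per arm: 72.5% by the t calculation. This applies to an outcome judged at the first Bonferroni or Holm step.

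**The case against.** **The error rates depend on assumptions.** This stands. No correlations are given, 37% needs independence, and strong correlation brings the rate down to about 14%. It remains above 5% throughout the range examined.

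**The article never says that one positive result in nine means success.** This also stands. The aim can be read as three separate questions, each answered on its own, and whether error should then be controlled across outcomes is debatable. Even so, each question is tested at three visits, which gives about 12.5% per outcome at the between-visit correlation of 0.5. The absence of a stated rule is itself the gap: under the any-one rule the 5% fails, and under the all-three rule the 85% fails.

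**A reader might infer that a favourable visit could be picked and the rest left out.** The article does not support that. It commits to presenting all three follow-ups, to CONSORT reporting and to modelling all occasions together for each outcome. Only the emphasis is open. The joint modelling is listed as an additional analysis and carries no decision rule, so it does not control the error either.

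**A multiplicity procedure may sit in an analysis plan that is not shown.** The missing procedure alone would be a weak point. But the article itself fixes the three primary outcomes, the separate tests by visit, the 5% level and a single-test sample size, and these do not fit together as they stand.

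**Conclusion.** The point holds. As written, the primary analysis is nine tests at 5%, with no primary follow-up for effectiveness and no rule linking the results to the primary aim. The sample size is correct for one test.

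If any single significant result counted, the family-wise error would be about 14-33% under the correlations assumed here and 37% under independence. For three outcomes at one visit it would be about 11-14%. It would be wrong to read any of these as the trial's actual error rate, because they depend on assumed correlations and on a success rule that the article does not state. The mismatch between the primary definition, the 5% level and the single-test power depends on neither assumption.

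**What to change.** Before outcome data are unblinded, name one follow-up as primary for effectiveness. Four months is one reasonable choice, since it is already the primary economic horizon, but that is not in itself a clinical argument and the trial team may prefer another visit. Then choose one of two rules:

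1. **Fixed sequence.** Test FAI fatigue severity, the basis of the sample size, first at two-sided 5%. If it is significant, test MS-FSE and then MSIS-29 total at the same visit, each at 5%. The stated single-test power for fatigue is kept and no extra participants are needed.
2. **Co-equal outcomes.** Keep all three and apply Holm across them at the primary visit. Restate the power: about 72% at 73 per arm for an outcome at the first step, against the stated 85%.

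Under either rule, report the other two visits as secondary, with estimates and confidence intervals.

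The cost is more than wording. Under the sequence, two outcomes now called primary become claims that depend on the fatigue result. Under both rules, a significant result at another visit is only supportive.
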